### Participants

Eligible participants are 9 to 12-years-old at study enrollment, have a BMI at or greater than the 85th percentile for age and sex, and have one or more of the following T2D risk factors: ethnic minority, first or second degree relative with T2D, conditions associated with insulin resistance or metabolic syndrome (including acanthosis nigricans, hypertension, dyslipidemia, polycystic ovarian disease, small for gestational age birth weight, maternal history of gestational diabetes [17]). Eligible children must also have a primary caregiver willing to participate in intervention sessions and activities (note: primary caregiver is an adult who most frequently prepares/obtains food, regulates media use, and provides physical activity opportunities for the child), be willing to use a study-provided mobile device throughout intervention, and speak and read English. Exclusion criteria are previously diagnosed Type 1 or Type 2 diabetes mellitus (this is not an exclusion criteria for the caregiver), psychiatric disturbances or mental illness, limitations preventing physical activity, or using medications known to cause weight loss or gain or affect appetite.

Participants will be recruited through pediatric and family medicine practices, the Southern Arizona YMCA membership, and the Tucson community (e.g., libraries, community centers, public health department, and local health fairs) using electronic announcements, flyers, posters, and word-of-mouth between May and August 2015, and between October 2015 and January 2016. Respondents will be invited to attend study information sessions held at participating YMCA locations where eligibility will be confirmed. Interested and eligible respondents will complete the informed consent process following University of Arizona Institutional Review Board-approved materials and methods and assigned a study location based on geographical proximity. Written consent will be obtained from parents; verbal assent will be obtained from youth and documented in writing by study staff. Families who are not yet YMCA members will be provided access to YMCA facilities free of charge for the duration of the study, with an opportunity to continue at a reduced rate after the study has concluded.

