## Procedures

### Randomization

Two YMCA sites, [A] and [B], were randomly assigned to face-to-face versus hybrid intervention formats using a random number table. Based on alphabetical order and an even number selected, [A] was assigned to receive the face-to-face format and [B] was assigned the hybrid format.

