Physiological outcomes will be assessed through 12-hour fasting insulin, glucose, and lipids drawn at J2 Laboratories, Tucson, Arizona, by a trained phlebotomist and placed into serum separator vacuum tubes. Insulin resistance (IR) will be assessed using HOMA [46], shown to more sensitive for identifying youth with metabolic dysregulation than an impaired fasting glucose threshold [47]. Calculation of IR is based on modeling of fasting insulin and glucose concentrations using the formula: fasting insulin (μU/ml) × fasting glucose (mmol/L)/22.5 = HOMA. HOMA correlates closely to IR as measured by euglycemic clamp [48], and a HOMA insulin resistance value of 2.6 will be used as the upper limit of normal [49]. Blood pressure will be measured on the non-dominant arm using an automatic monitor (Omron HBP-1300, Hoofddorp, The Netherlands) and cuff-sizes appropriate for the mid-upper arm circumference. Systolic and diastolic blood pressure will be measured two times with 5 min intervals while the participant is seated and resting. The definition of hypertension will be adjusted for age per national guidelines [50]. Individuals with fasting glucose values >126 mg/dL and no previous history of T2D will be referred to their primary care provider. The study medical director will be immediately informed and arrange appropriate follow-up depending on the level of blood glucose elevation and symptoms. Maturity will be assessed using Tanner’s validated self-report questionnaire which presents illustrations of developmental stages shown to agree with pubertal staging by a physician [51, 52].

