### Statistical analysis

Outcome measures will be stratified by delivery format to assess whether the mobile technology-supported delivery of the intervention is as efficacious as the face-to-face format. Descriptive statistics for change in endpoints (mean, median, and standard deviation) between baseline and 12-week measurements will be computed separately for each program format (face-to-face or hybrid mobile technology-supported program). The statistical significance of the change at 12 weeks will be assessed using a paired t-test combining both formats. One-sided statistical tests will be used, as the interventions approaches are of interest only if they decrease the percentage overweight and lead to improvements in diabetes risk factors. Statistical significance is set at alpha = 0.05. Sample size constraints do not allow adequate statistical power to formally test for differences between the two formats. However, exploratory models using linear regression analysis will estimate the magnitude of the difference between the face-to-face and combined formats, adjusted for baseline levels and the potential correlation between the participants within a given YMCA (expected to be small). These parameter estimates will provide effect sizes to appropriately power a larger study comparing the two formats. Since this is a randomized comparison, confounding is not an issue as long as there is non-differential dropout between the two formats. Differential dropout between the two formats will be assessed using a Fisher’s Exact Test. Similar analyses will assess whether improvements are maintained after the intervention ends, by comparing the 24-week versus 12-week values. We acknowledge the potential for differential loss to follow-up and missing data. Baseline values of those who complete the study versus those who do not will be compared using two sample independent t tests and Fisher’s Exact Tests, as appropriate. Additional sensitivity analyses will use multiple imputation for missing values and an intent-to-treat analysis with baseline values carried forward.

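### The format comparison is declared free of confounding because it is randomized, but only two sites were randomized and families were placed by proximity, so format cannot be separated from site and child-level differences are possible

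*Protocol article*

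**What the plan says.** All references are to the protocol article.

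- **Model.** Statistical analysis describes exploratory linear regression of the format difference, "adjusted for baseline levels and the potential correlation between the participants within a given YMCA". It names no other covariate. (It calls the second format combined; the Abstract shows that hybrid is meant.)
- **Reason given.** The same section states: "Since this is a randomized comparison, confounding is not an issue as long as there is non-differential dropout between the two formats".
- **What was randomized.** Randomization: "Two YMCA sites, [A] and [B], were randomly assigned to face-to-face versus hybrid intervention formats".
- **How families reach a format.** Participants: eligible families are "assigned a study location based on geographical proximity".
- **Maturity.** Data collection: "Maturity will be assessed using Tanner’s validated self-report questionnaire". Statistical analysis gives it no use.
- **Timing.** Participants: recruitment runs "between May and August 2015, and between October 2015 and January 2016". No wave variable is listed.
- **Standing of the comparison.** Statistical analysis: "Sample size constraints do not allow adequate statistical power to formally test for differences between the two formats". The estimates are meant to supply effect sizes for a larger trial of the two formats.

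**The concern.** Randomization guards against confounding for the units that were randomized, and only when there are enough of them. Here there are two units, one in each format, and the children in each were gathered by residence. Nothing in the design balances pubertal stage, family circumstances or neighbourhood between formats. Equal dropout, the only condition that the plan attaches, does not repair this.

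Pubertal stage is the clearest measured example. The children are 9 to 12 years old and followed for 24 weeks. Percent overweight is standardized for age and sex, but HOMA and waist circumference are not. Adjusting for baseline HOMA does not necessarily remove a difference between stages in how HOMA changes.

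The format estimate is to be carried into the sample size of a later trial. If it is read as unconfounded, a site difference could enter that calculation as a format effect.

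**Working it through.** **What the plan's figures give.** No figure is stated for the format regression. The evaluable number reproduces: 60 × (1 − 0.20) = 48, or 24 per site if dropout is even. Intercept, format and baseline leave 48 − 3 = 45 residual degrees of freedom.

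**Step 1: can the YMCA correlation be adjusted for?** Two sites minus two format means leaves 0 degrees of freedom for between-site variance. As a rank check, a design matrix with intercept, format, baseline and site has 4 columns and rank 3. Adding four Tanner indicators and one for wave gives 9 columns and rank 8. Format and site remain one column.

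**Step 2: size of the site component.** The intraclass correlation (ICC) and the SD of change are not in the document, so both are assumed. Two SDs are used:
- 7.6 points: 1.1 × √48, treating the quoted SE of 1.1 as if it came from 48 children.
- 11.98 points: 4.3 × √48 / (1.645 + 0.842), the SD at which 48 children give 80% one-sided power.

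The difference between two site effects has SD = SD × √(2·ICC). The variance of the format difference that ignores site is SD² × (2/24)(1 − ICC); the full variance adds SD² × 2·ICC.

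| ICC | Site component, SD 7.6 | Site component, SD 11.98 | Coverage of nominal 95% interval |
|---|---|---|---|
| 0.01 | 1.1 points | 1.7 points | 92% |
| 0.02 | 1.5 points | 2.4 points | 89% |
| 0.05 | 2.4 points | 3.8 points | 81% |

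Coverage is 1 minus the two-sided exceedance probability (0.079, 0.108, 0.193) when the SE that ignores site is used.

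**Step 3: measured child-level imbalance.** Bias = difference in mix × effect. Every input is assumed.
- Tanner: a 30-point gap in mid or late puberty and a 0.5 SD effect on change in HOMA give 0.30 × 0.5 = 0.15 SD. Half the gap gives 0.075 SD; no gap gives 0. The SE is √(2/24) = 0.29 SD, so the largest of these is about half an SE.
- Wave: a 2-point effect with a 40/60 v 60/40 mix gives 0.20 × 2 = 0.4 points. The SE is 7.6 × 0.29 = 2.2 to 11.98 × 0.29 = 3.5 points. With equal mix the bias is 0.

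**Step 4: does adjustment improve precision?** SE ratio = √[(1 − R²) × (df before / df after) × VIF], where R² is the residual variance explained and VIF is the variance inflation from the correlation of the covariates with format.
- Balanced Tanner and wave (2 df, VIF 1): √(0.9 × 45/43) = 0.970 and √(0.8 × 45/43) = 0.915 for R² of 10% and 20%.
- With the imbalance of step 3: the correlations with format are about 0.30 for stage (35% v 65%) and 0.20 for wave. If stage and wave are uncorrelated, VIF = 1/(1 − 0.09 − 0.04) = 1.15, and the ratios become 1.04 and 0.98.
- Tanner alone (1 df) at the step 3 values: the within-format variance of stage is 0.35 × 0.65 = 0.2275, so R² = 0.5² × 0.2275 = 0.057 and VIF = 1/(1 − 0.09) = 1.10. The ratio is √(0.943 × 45/44 × 1.10) = 1.03.

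The imbalance that makes adjustment worthwhile also removes most or all of the gain in precision.

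**The case against.** The strongest case against the point is that a longer covariate list for an exploratory, unpowered model is routinely left to the analysis plan, which is not shown. With about 48 children a short list is defensible. The primary outcome is already standardized for age and sex, and baseline is adjusted for. It is also formally true that sites were allocated at random, so over repeated allocations the estimator is not systematically biased.

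Much of this stands. The absence of Tanner stage from the described model would not be a finding by itself. What remains is that the article does more than leave the list open: it fixes an adjustment set and supports it with a reason that its own Randomization and Participants sections contradict. Random allocation of two sites gives no protection in the one allocation that occurred, and it gives no means of estimating the error.

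Some stronger readings are tempting but not supported:
- **That recruitment wave is recorded and confounds format.** Two windows are given for the whole study. Wave could be derived from enrolment date, but no difference in wave mix between sites is stated or implied.
- **That the format estimate is known to be biased.** No imbalance is documented; it is only possible.
- **That adding covariates sharpens the estimate by 3% to 9%.** That range needs balanced covariates (step 4).
- **That covariates cure the confounding.** They address measured child-level differences only. Differences in site, neighbourhood and coaches remain.

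**Conclusion.** The point holds in a limited form. The statement that confounding is not a concern is wrong for two sites, one per format, filled by residence. The within-YMCA correlation cannot be estimated from these data, and format cannot be separated from site under any patient-level adjustment.

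Adjusting for Tanner stage would remove measured imbalance in maturity, mainly for physiological outcomes. On the assumed inputs that is at most 0.15 SD, about half a standard error, and less to the extent that baseline adjustment already captures it. The site component could be 1.1 to 3.8 points, conditional on the assumed ICCs and SDs. The plan itself expects the correlation to be small, which points to the lower end.

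The importance is modest. The formats are not formally tested, and the primary paired t-test pools both formats and is unaffected. The matter counts because the format estimates are intended to size a later trial.

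**What to change.** 1. In Statistical analysis, withdraw the sentence that rules out confounding. Say instead that two sites were randomized, one per format, that families were placed by proximity, and that the format difference is descriptive and inseparable from site.
2. Say that the between-YMCA correlation cannot be estimated with one site per format. For planning the larger trial, take it from outside data or present a range.
3. Beside the planned model, report one that adds baseline Tanner stage, grouped (for example 1–2 v 3–5), plus age and sex for outcomes not standardized for them, such as HOMA. The article does not say at which visit maturity is assessed, so specify the baseline value.
4. Tabulate enrolment window by site. Add wave, derived from enrolment date, only if its mix differs.
5. Claim no precision gain, and do not present the adjusted model as removing the site effect.

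The cost is wording and one additional model, with no new data. Grouped Tanner stage uses 1 degree of freedom, age and sex 2 more, and wave 1 more, leaving 44 to 41 of the 45. Ungrouped Tanner stage (four indicators) with wave would leave 40, which is a reason to group.

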**Methods/Design:**

Using participatory methods, the adult-focused YMCA Diabetes Prevention Program was adapted for families, creating a novel lifestyle behavior change program focused on healthy eating, physical activity, and a supportive home environment. The program will be tested in sixty 9- to 12-year-old children at risk of diabetes and sixty parents over 12 consecutive weeks with two intervention formats randomized by location: a face-to-face instructor-led program, or a hybrid program with alternating face-to-face and mobile technology-delivered content. Anthropometric, behavioral, psychosocial and physiological outcomes will be assessed at baseline, post-intervention (12 weeks), and follow-up (24 weeks). Secondary outcomes are participant acceptability, feasibility, and adherence. The RE-AIM framework (reach, efficacy, adoption, implementation, and maintenance) will guide intervention implementation and evaluation. Changes at 12 weeks will be assessed using a paired t-test combining both delivery formats. Exploratory models using linear regression analysis will estimate the magnitude of the difference between the face-to-face and hybrid format. The sample size of 60 children, informed by a previous YMCA intervention in which −4.3 % change in overweight (SE = 1.1) was observed over 6 months, will give us 80 % power to detect an effect size of this magnitude, assuming a one-sided test at alpha = 0.05.

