## Methods/Design

### Study design

The impact of the EPIC Kids intervention will be evaluated using a group-randomized, non-inferiority trial design with three data collection points: baseline, post-intervention (immediately post program completion at 12 weeks), and follow-up (24 weeks) (Fig. 1). The program will be tested with sixty, 9- to 12 year-old children and their parent(s) or primary caregiver(s) at two YMCA locations in Tucson, Arizona where families lack services and resources needed for T2D prevention. Randomization to delivery formats will occur by YMCA location to minimize between-group contacts. One site will conduct a face-to-face weekly YMCA lifestyle coach-led program, while the second site will host a program equivalent in duration, frequency, and content, also lead by YMCA coaches, but with 5 weeks (40 %) of content digitally delivered using study-provided mobile devices (Kindle Fire HDX7, Amazon). Thirty families will be recruited to participate in each intervention format; each family will be assigned to an intervention group led by two trained YMCA lifestyle coaches and consisting of up to 9 other families. Weekly sessions will occur over 1.5 h for 12 weeks.

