### Sample size and power

The primary outcome is change in percent overweight. Our estimated sample size was informed by the results of Foster et al. [18] who observed a mean decrease of 4.3 % in percentage overweight (SE = 1.1) in a YMCA-based pediatric obesity intervention over 6 months, and is based on the number of participants needed to detect an effect size of this magnitude with 80 % power assuming a one-sided test at alpha = 0.05. Given a final sample of 48 children and allowing for up to 20 % attrition, 60 participants will be recruited.

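### The pilot's between-format estimate cannot supply the effect size for a larger trial: format is inseparable from site, and about 24 completers per format give a 95% half-width near 0.58 SD

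*Protocol article*

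**What the plan says.** The Statistical analysis section concedes that the sample is too small for a formal test between formats. It then plans exploratory linear regression, adjusted for baseline and for correlation among participants at the same YMCA, and gives the result a planning role: "These parameter estimates will provide effect sizes to appropriately power a larger study comparing the two formats". The same section says that randomization removes concern about confounding, provided dropout does not differ between formats.

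The design behind that estimate is set out elsewhere in the article:

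- Randomization: "Two YMCA sites, [A] and [B], were randomly assigned to face-to-face versus hybrid intervention formats using a random number table".
- Participants: families are "assigned a study location based on geographical proximity".
- Study design: "Thirty families will be recruited to participate in each intervention format".
- Sample size and power: "Given a final sample of 48 children", and "allowing for up to 20 % attrition, 60 participants will be recruited".

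The contrast is named in two ways. The Statistical analysis section will "estimate the magnitude of the difference between the face-to-face and combined formats"; the Abstract will "estimate the magnitude of the difference between the face-to-face and hybrid format".

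**The concern.** The sentence claims a property that the design lacks. An estimate that is to size the next trial must isolate the format effect and be reasonably precise. This one does neither. It carries any difference between the two sites, their catchments and their coaches, and its interval is wide relative to any plausible difference between two versions of the same programme.

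The concession about power covers formal testing only. It does not cover use of the point estimate for planning, which is what the next sentence announces. The confounding statement adds to the problem because it tells the reader that site differences can be ignored. At stake is the sample size of the follow-on trial, not any conclusion of this one.

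**Working it through.** **The plan's own figure.** 48 / (1 − 0.20) = 60, which reproduces the recruitment target. With 30 families per format and equal attrition (assumed), 30 × 0.80 = 24 completers per format.

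**Site and format.** There are two sites, one per format. Between-site degrees of freedom within format: (1 − 1) + (1 − 1) = 0. Variation between sites cannot be estimated from these data, so the within-YMCA adjustment has nothing to work with. Tossing a coin between two sites is fair beforehand, but the one realised comparison contains the whole site difference, and more children per site would not reduce it. If the within-site correlation were 0.02 or 0.05 (assumed; the article says only that it should be small), the chance difference between two sites would have a standard deviation of √(2 × ICC) = 0.20 or 0.32 SD, however many children were enrolled.

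**Precision, ignoring site.** SE = SD × √(2/24) = 0.289 SD. With 46 degrees of freedom the 95% half-width is 2.013 × 0.289 = 0.58 SD.

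The article gives neither an SD nor the test behind n = 48. Two readings bound a range:

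- One-sided paired test, 0.05, 80% power, n = 48: SD = 4.3 × √48 / (1.645 + 0.842) = 12.0 (11.8 with the exact t).
- Two groups of 24, same error rates: SD = 4.3 / (2.487 × 0.289) = 6.0.

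| Assumed SD | SE (points) | 95% half-width (points) |
|---|---|---|
| 6 | 1.73 | 3.5 |
| 8 | 2.31 | 4.7 |
| 10 | 2.89 | 5.8 |
| 12 | 3.46 | 7.0 |

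The planned total pre-post change is 4.3 points.

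**With clustering.** Using the design effect 1 + 23 × ICC and the normal quantile, the half-width rises from 0.57 SD at ICC 0 to 0.68 SD at ICC 0.02 and 0.83 SD at ICC 0.05 (ICCs assumed).

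**Illustration for a superiority trial.** Suppose the true difference is 0.3 SD (assumed). At two-sided 0.05 and 80% power, n per arm = 2 × (1.960 + 0.842)² / 0.3² ≈ 175 before clustering. The middle half of pilot estimates, 0.3 ± 0.6745 × 0.289, runs from 0.11 to 0.49 SD. Entered in the same formula unrounded, these limits give 1416 down to 65 per arm. About 15% of pilot estimates would have the wrong sign (0.3/0.289 = 1.04 standard errors from zero).

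**What the pilot can inform.** With 46 degrees of freedom, the 95% CI for the SD of change is about 0.83 to 1.26 times the estimate, which is usable. Correlation within coach-led groups is a different matter. Intervention delivery allows at most three groups per site, so six in all, or 48/6 = 8 completers each. At an observed ICC of 0.05, F = (1 + 7 × 0.05)/(1 − 0.05) = 1.42 on 4 and 42 degrees of freedom, and the 95% CI for the ICC is about −0.07 to 0.58.

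**The case against.** The strongest defence is that the limitation is largely disclosed. The models are labelled exploratory, low power is admitted, the sentence concerns a future study, and the primary analysis is a pooled paired t-test that does not use the coefficient. This stands as a limit on severity. It does not rescue the sentence, which makes a positive claim about planning.

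A second defence is that the size depends on assumptions, and this stands too. A reader might infer that the interval is necessarily wider than the whole expected programme effect. The article does not support that: with no SD given, the half-width is below 4.3 points at SD 6 and above it at SD 8 or more. Baseline adjustment would also narrow the interval by an unknown amount, though it would not remove site. What holds at any SD is 0.58 SD before that adjustment.

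Third, Study design labels the trial non-inferiority and Anticipated results expects the formats to be comparable. If the larger study is also non-inferiority, a margin and an SD drive its size, and the superiority illustration does not describe it. That weakens the illustration, but it also weakens the case for taking an effect size from the pilot.

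Finally, a reader might take the word combined literally and infer that face-to-face will be compared with a pool containing it, which would halve the difference. The surrounding sentences speak of two formats and the Abstract names hybrid, so this is evidently a slip, and no numerical consequence follows.

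**Conclusion.** The point holds. The between-format coefficient cannot appropriately size a larger study, because it is format plus site and because its 95% half-width is about 0.58 SD even when site is ignored. The site argument needs no assumption; it follows from one YMCA per format. The precision figure assumes equal attrition and no baseline adjustment, and its translation into 3.5 to 7.0 points assumes an SD between 6 and 12.

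The consequence is that a trial sized on this estimate could be badly over- or under-powered; the article does not show that it would be. Nor does it show that any observed difference would be purely a site effect, only that the two could not be told apart. The change should be made, but it concerns a claim about later use and leaves this trial's primary result untouched.

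**What to change.** In the Statistical analysis section:

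1. Delete or restate the sentence on powering a larger study, so that the pilot informs the SD of change, retention and recruitment, each with a confidence interval.
2. Report the format coefficient with its 95% CI as descriptive, and state that it cannot be separated from site.
3. Qualify the confounding statement in the same way: with two sites, randomization does not rule out site differences.
4. State that the larger study will rest on a substantively chosen difference or non-inferiority margin, and on an external range for the within-cluster correlation. Any correlation from the six or fewer coach-led groups should be reported only with its CI and not used alone.
5. Replace combined with hybrid in the description of the contrast, to match the Abstract.

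No data collection or primary analysis changes. The cost is a more modest claim for the pilot.

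### For the pooled 12-week test, carrying baseline forward nearly reproduces the completers' p-value, so it adds almost nothing as a check on attrition bias

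*Protocol article*

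**What the plan says.** All references are to the protocol article. Under Sample size and power, "The primary outcome is change in percent overweight". The same section plans a final sample of 48 children and recruits 60, to allow for up to 20% attrition.

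Under Statistical analysis, "The statistical significance of the change at 12 weeks will be assessed using a paired t-test combining both formats". The tests are one-sided and "Statistical significance is set at alpha = 0.05". Because the formats are pooled, the primary test is in effect a single-group before-after comparison.

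The same section acknowledges differential loss and missing data, and plans four things in response:
- a Fisher's exact test of differential dropout between the formats;
- a comparison of baseline values between completers and non-completers;
- multiple imputation as a sensitivity analysis;
- a second sensitivity analysis, described as "an intent-to-treat analysis with baseline values carried forward".

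Maintenance after the programme is assessed with similar methods, "by comparing the 24-week versus 12-week values".

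**The concern.** A sensitivity analysis for missing data is useful if its answer can differ from the main one when the missing children differ from those observed. Carrying baseline forward in a before-after test fills each gap with a change of zero. That lowers the mean change, and so looks cautious, but it also lowers the variability and raises the sample size. If these effects cancel, the p-value is that of the completers under another name. The intent-to-treat label then suggests a protection that the calculation does not give.

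Up to one child in five may be lost, and the primary test has no control group against which dropout could be balanced. If families who leave do worse than those who stay, the completer analysis overstates the benefit, and this check would not show it.

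**Working it through.** **Inputs from the protocol article.** Completers n = 48, recruited N = 60, mean decrease 4.3 (SE 1.1) in the cited YMCA study, one-sided alpha 0.05, power 80%.

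**Input that is an assumption.** No SD of change is given. An SD of 11.81 gives 80% power with 48 children by the t-distribution; the normal approximation gives 11.98. If the SE of 1.1 came from about 48 children, the SD would be 1.1 × √48 = 7.62. These values serve as a range below.

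**The plan's own figure.** 48 / (1 − 0.20) = 60. It reproduces.

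**Step 1: general result.** Let the completers have mean change d, SD s and t = d / (s/√n). Add N − n zeros.
- Mean: (n/N) × d.
- Sum of squares about the new mean: (n − 1)s² + n·d²·(1 − n/N) = s²[(n − 1) + t²(1 − n/N)].
- New statistic: t_B = t × √{ n(N − 1) / ( N[(n − 1) + t²(1 − n/N)] ) }.

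Only t, n and N appear. Neither the SD nor anything about the dropouts enters.

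**Step 2: with 48 of 60.**

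| Completers' t | p | t with baseline carried forward | p |
|---|---|---|---|
| 1.678 (critical value) | 0.0500 | 1.672 | 0.0500 |
| 2.00 | 0.0257 | 1.987 | 0.0258 |
| 2.487 | 0.0083 | 2.460 | 0.0084 |
| 3.909 (= 4.3/1.1) | 0.00015 | 3.796 | 0.00017 |

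At the boundary the p-value stays at 0.050 for any attrition from 5% to 40%.

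**Step 3: worked example, SD 11.81.**
- Completers: SE = 11.81/√48 = 1.705; t = 4.3/1.705 = 2.52; p = 0.0075.
- Baseline carried forward: mean = 48 × 4.3/60 = 3.44; SD = √[(47 × 11.81² + 48 × 4.3² − 60 × 3.44²)/59] = 10.68; SE = 10.68/√60 = 1.379; t = 3.44/1.379 = 2.49; p = 0.0077.
- The mean falls by the factor 0.80 and the SE by 1.379/1.705 = 0.81.

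**Step 4: what the dropouts could do to the result.** Suppose the 12 dropouts gained g points on average, with the same SD as completers. The gains are assumptions. The overall mean decrease is (48 × 4.3 − 12g)/60.

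| g | Overall mean decrease | p, SD 11.81 | p, SD 11.98 | p, SD 7.62 |
|---|---|---|---|---|
| 4 | 2.64 | 0.049 | 0.051 | 0.008 |
| 6 | 2.24 | 0.084 | 0.087 | 0.024 |
| 8 | 1.84 | 0.13 | 0.14 | 0.060 |

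Baseline carried forward gives one answer for every row of a column: p = 0.0077, 0.0084 and 0.0002 respectively.

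**Step 5: simulated error rates** (50,000 runs, SD 11.98; assumed true mean change of zero across all 60). If dropouts are worse than completers by 0.5, 1.0 or 1.5 SD, the false-positive rate is 17.0%, 38.9% or 65.9% for completers, and the same to one decimal with baseline carried forward. Complete data on all 60 would give 4.7%, 3.6% or 2.8%.

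**Step 6: 24 versus 12 weeks.** If the rule is applied literally here, a child missing at both visits has baseline minus baseline, which is zero and counts as full maintenance. A child seen at week 12 and lost afterwards has baseline minus the 12-week value, which is a full return to baseline. One rule thus makes opposite assumptions according to when the child left.

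**The case against.** The strongest reply is that this is one of two additional sensitivity analyses, and that the article does more than this about dropout: it plans multiple imputation, compares completers with non-completers at baseline, and tests differential dropout between formats. That is correct, and a reader who inferred that the plan has no other handling of missing data would be wrong. What remains is that standard multiple imputation assumes missing at random, and that neither comparison can show outcomes that were not observed.

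A second reply is that the estimate does fall by a fifth, from 4.3 to 3.44. It does, but by a factor set by the dropout rate alone, so the fall says nothing about bias.

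A reader might also infer that the check can never change any result. The documents do not support that. The near-identity belongs to the pooled 12-week test. It does not carry over unchanged to the 24- versus 12-week comparison, where a late dropout counts as full relapse, or to the exploratory regression between formats. Nor does the article say that a completer result would be reported as confirmed by this analysis.

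The illustration also has limits. The outcome is measured against the median BMI for age and sex, so ordinary growth is already allowed for, and the article gives no figure for an untreated rise. At SD 11.81 a 4-point gain leaves the result just significant. The 6-point case needs dropouts to differ from completers by 10.3 points, and bringing the overall mean to zero would take a gain of 48 × 4.3/12 = 17.2 points.

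Finally, a tipping-point analysis might be left to an analysis plan that is not shown. The point here is that the method the article does state is a poor one for its purpose.

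**Conclusion.** The point stands in a limited form. For the pooled 12-week paired t-test, baseline carried forward repeats the completers' significance verdict almost exactly. At 48 of 60 the t-statistic keeps 99.6% of its value at the critical value and 97.1% at t = 3.909, and simulated verdicts differ in about 0.01% of trials at the planned power. This follows from t, n and N alone and needs no assumption about the SD. The p-values for worsening dropouts do depend on the assumed SD and gains: significance is lost at a gain of about 4 points if the SD is 11.8 to 12, and between 6 and 8 points if it is 7.62.

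The primary test, its endpoint and the sample size are not affected. The finding does not show that attrition bias will occur. It shows that this analysis would not detect it at 12 weeks, and that the other planned analyses, as described, do not let dropouts do worse than missing at random implies. The change is a cheap and worthwhile improvement.

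**What to change.** Replace the baseline-carried-forward analysis with a delta-adjusted version of the multiple imputation already planned. Worsen the dropouts' imputed percent overweight in fixed steps, repeat the paired test at each step, and report the step at which significance is lost. Continue the steps until that happens. If imputation centres dropouts near the completers' mean (an assumption), a 4-point gain from baseline corresponds to a shift of about 4.3 + 4 = 8.3 points, so a grid that stops at 8 could end too early.

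If baseline carried forward is kept, describe it as a single-imputation analysis, do not offer it as evidence of robustness to dropout, and state how it applies to the 24- versus 12-week comparison. A repeated-measures model using all available visits is optional. It too assumes missing at random and does not by itself solve this problem.

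The cost is a change of wording, modest extra programming, and a sensitivity result that may be less favourable.
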